### C*oping-Together* and minimal ethical care (MEC) conditions

At recruitment, participants will be informed that they will be mailed one of two resources, without knowing which one is the study intervention. *Coping-Together* couples will receive the intervention material previously described within 2 weeks of returning a baseline survey (see Figure 2 – study timeline). One to two weeks thereafter, a member of the research team will phone them to orient them to *Coping-Together*. The intent of this brief orientation call (anticipated duration = 20 minutes) will be to ensure participants received the material, provide an overview of the content, and explore intended use of the resource. Couples will then receive, fortnightly, a 'Top Tips' sheet highlighting timely content of the booklets and a follow-up, telephone call (anticipated duration = 20 minutes) from a member of the research team to monitor the use of *Coping-Together* and other resources and answer questions pertaining to the materials received. Although the calls will be conducted by experienced, trained research assistants, the research assistants will not provide counseling, as they are not registered therapists. A script will be developed to guide the discussion.

**Figure 2 F2:**
[figure not shown]
Study Timeline.

As MEC couples also have elevated distress, and to blind participants to group allocation, this study will not employ a ‘no treatment’ control group. MEC couples will be mailed booklets from the ‘Understanding Cancer Series’ available at the Cancer Council New South Wales and a Cancer Council Helpline brochure, and will also receive initial and follow-up phone calls, comparable in intent and content to the one described for *Coping-Together* couples. All phone calls will be audio-recorded and coded to monitor topics discussed across intervention participants and ensure that counselling was not provided.

### Blinding

Participants will be told they will receive one of two information packs, but as they do not know which one is the study intervention and the study survey and contact with the research team is comparable across groups, they are blinded to whether they are in the MEC or *Coping-Together* group. The participants will also be blinded to study hypotheses. As it is expected that couples will mainly use *Coping-Together* at home, the chance of MEC participants being exposed to the intervention is minimal.

All contact with the couples will occur through the same research assistant(s) who will not be blinded to group allocation and will assign a study ID, randomise participants, send study packs, and conduct follow-up phone calls. A separate research assistant, who will have no contact with participants and will be blinded to group allocation, will enter the data. The chief investigators and the statistician will not be able to link study IDs (and surveys) back to a recruitment site or group and are therefore blinded to group allocation.

### Outcomes

As the development of *Coping-Together was* guided by the Lazarus & Folkman’s Stress and Coping framework (see Figure 1) [67], outcomes selected either characterise the coping process (appraisal, dyadic and individual coping strategies, and self-efficacy) or indicate the extent to which the coping process was successful in addressing stressors (anxiety, cancer distress, depression, quality of life, and relationship satisfaction).

#### Measures

Table 1 lists the primary and secondary outcomes and corresponding measures.

**Table 1 T1:** ***Coping-Together *****study outcomes and measures **

**Outcomes**	**Measures and Psychometrics**
**Primary Outcome**	
**Anxiety**	7-item HADS-Anxiety Subscale (patients and partners) [69] (α = .68-.93) [70]
**Secondary Outcomes**	
**Depression**	7-item HADS-Depression Subscale (patients and partners) [69] (α = .67-.90) [70]
**Cancer distress**	15-item Revised Impact of Event Scale (patients and partners; α = .78-.96) [71]
**Quality of Life (QOL)**	35-item Assessment of Quality of Life – 8 Dimensions Scale (AQoL-8D; patients and partners) [72]
	35-item Caregiver’s QOL Index-Cancer (partners) [73]
**Relationship satisfaction**	7-item Spanier Dyadic Adjustment Scale (patients and partners) [74] α = .89-.95) [75]
**Appraisal**	28-item Kessler Cognitive Appraisal of Health Scale (patients and partners [adapted]; α > .70) [76]
	33-item Mishel’s Uncertainty Scale (patients and partners; α = .64-0.91) [77]
	27-item Appraisal of Caregiving Scale (partners; α > .85) [78,79]
S**elf-efficacy**	17-item Cancer Self-Efficacy Scale (patients and partners; α = .97) [78]
	12-item Communication and Attitudinal Self-Efficacy Scale for Cancer (CASE-Cancer; patients and partners [adapted]; α = .76-.77) [80]
**Dyadic coping**	37-item Dyadic Coping Inventory (patients and partners; α = .63-.84) [81]
**Individual Coping**	28-item Brief COPE measures 14 individual-level coping strategies (patients and partners; α = .60-.90) [82]
**Moderators***	
**Information obtained and information-seeking preferences**	25-item EORTC Quality of Life (QOL) – information module (patients and partners; α > 0.70) [83]
	45-item Profile of Preferences for Cancer Information (PPCI) (patients and partners [adapted]) [84]
**Readiness for self-directed learning**	39-item adapted version of the Learning Preference Scale (patients and partners [adapted]) [85]
**Problems experienced**	48-item adapted version of SupportScreen scale (patients and partners [adapted]) [86]

*Note.* Brackets indicate if patients and/or partners will complete the measure. * Questionnaires measuring potential moderators were included in the survey to reflect those that would be included in a survey for a larger trial to comprehensively examine the feasibility of the methods. However, the pilot is underpowered and moderators will not be analysed.

*Initial distress screening*: At the time of recruitment, the single-item DT will be used to screen patients’ level of distress. The DT asks patients to circle the number that best describes their overall distress using a visual analogue scale ranging from 0 = ‘no distress’ to 10 = ‘extreme distress’ [36]. The DT has convergent validity with the Hospital Anxiety and Depression Scale (HADS) [36], with a cut-off point of four typically resulting in optimal sensitivity and specificity [68].

*Primary outcome: Anxiety* is the primary outcome, as *Coping-Together* focuses on coping strategies to manage high levels of anxiety directly and/or cope with cancer demands known to trigger anxiety. *Anxiety* will be measured using the 7-item anxiety subscale of the Hospital Anxiety and Depression Scale (HADS-A) [69]. HADS-A is a reliable and valid measure of the severity of anxiety for patients with cancer and their partners and is often considered the ‘benchmark’ for validation of other anxiety measures [87-90].

#### S*econdary outcomes*

*Depression* will be measured using the 7-item depression subscale of the Hospital Anxiety and Depression Scale (HADS-D) [69].

Cancer specific *distress* will be measured with the Revised Impact of Event Scale [71].

*Quality of Life* (QOL) will be measured with the Assessment of Quality of Life – 8 dimensions (AQoL-8D). The AQoL8D is a newly developed health-related QOL instrument specifically for use with people with mental health problems and distress [72]. Also, the Caregiver’s QOL Index-Cancer will be used to assess caregiver’s mental and emotional burden, life disruption, positive adaptation and financial concerns [73].

*Relationship satisfaction* for partners and caregivers will be measured using the Spanier Dyadic Adjustment Scale (dyadic consensus, satisfaction, cohesion, and affective expression) [74], which is a widely used measure of satisfaction with intimate relationships.

*Primary illness appraisal* will be measured by the Kessler’s Cognitive Appraisal of Health Scale [76], Mishel’s Uncertainty in Illness Scale [77], and the Caregiving Illness Appraisal Scale [78,79].

*Secondary illness appraisal (self-efficacy)* will be measured by the Cancer Self-Efficacy Scale [78] and the Communication and Attitudinal Self-Efficacy Scale for Cancer (CASE-Cancer) [80].

*Individual and dyadic coping* will be measured by the Brief COPE [82] and the Dyadic Coping Inventory [81].

#### Moderators

Although this pilot is underpowered to examine the differential impact of the intervention across participant sub-groups, the pilot survey will include all measures that would potentially be considered for a larger trial to comprehensively examine the feasibility of the methods.

*Information obtained and information-seeking preferences* will be measured by the EORTC Quality of Life (QOL) – information module [83] and a tool developed by the first author – The Profile of Preferences for Cancer Information (PPCI) [84,91], respectively.

A cancer care diary developed by members of the research team will also be completed for the duration of the study to document *health professionals seen and health care resources utilised*.

*Readiness for self-directed learning* will be measured by items adapted from Guglielmino’s Learning Preference Scale [85].

*Problems experienced* will be measured by items adapted from the SupportScreen scale [86].

*Socio-demographic, disease and medical variables*, including date of diagnosis, treatment, symptom distress [92], age, and education, will also be measured.

### Data analysis

Intention-to-treat and per protocol analysis will be conducted separately for patients and partners. The primary outcome, anxiety (HADS-A) two months post baseline, will be analysed using ANalysis of COVAriance (ANCOVA). The main predictor variable in the ANCOVA model will be treatment group, and the participants’ baseline score will be included as a covariate. ANCOVA will also be used to explore the secondary outcome measures. Questionnaires measuring potential moderators were included in the survey to reflect those that would be included in a survey for a larger trial, and this contributes to a comprehensive examination of the feasibility of the methods; however, the pilot is underpowered and moderators will not be analysed.

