## Methods/design

### Design

The proposed study is a multicentre, stratified, double-blind, two-group, parallel, randomized controlled trial to compare *Coping-Together* to MEC. The design of this study was guided by the Medical Research Council framework for developing and evaluating complex interventions [56] and the CONSORT statement [57].

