### Randomization of group assignment

A computer-generated, randomization schedule with block lengths of variable size (4 and 6 couples) and stratified by recruitment source will be accessible to the main research assistant to allow assignment of a unique study ID to each couple as their consent forms/baseline surveys are received. Block randomisation is used to achieve balance in the allocation of couples across the MEC and *Coping-Together* groups and varying the block size reduces the chance of treatment allocation being known [66].

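### The stated ANCOVA omits recruitment source, the stratification factor; if source is prognostic beyond baseline, its intervals are wider than they need be

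*Protocol article*

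**What the plan says.** Three places in the protocol article bear on this point.

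- **Randomization of group assignment.** The schedule uses "block lengths of variable size (4 and 6 couples) and stratified by recruitment source". The Design section also calls the trial a "multicentre, stratified, double-blind, two-group, parallel, randomized controlled trial".
- **Data analysis.** The primary model is given as "The main predictor variable in the ANCOVA model will be treatment group", with each participant's baseline score as the covariate. The method is carried over to the other endpoints: "ANCOVA will also be used to explore the secondary outcome measures". Patients and partners are analysed separately, so each model has one record per couple.
- **Blinding.** "The chief investigators and the statistician will not be able to link study IDs (and surveys) back to a recruitment site or group".

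The article nowhere puts source into a model, and it does not describe a coded stratum variable for the statistician. It does not say how many strata there are. The Procedures section mentions urology practices in two states and advertising through media outlets.

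**The concern.** Stratified blocks hold the two arms nearly equal within each source. Differences between sources therefore largely cancel out of the treatment comparison, and the real sampling variation of the estimate falls. A model without source does not know this. It leaves the between-source variation in its residual and reports a standard error for a trial without stratification. If sources differ in two-month anxiety beyond what the baseline score explains, the reported interval is too wide for the design.

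What is at stake is precision. The Study aims section includes preliminary efficacy data as its second aim and expects trends rather than significance. The Implications section says the results will feed into a larger trial. An interval and residual variance that still contain source variation would describe the pilot's information as somewhat weaker than it is.

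**Working it through.** **Figures in the plan.** The article states no alpha, power, SD, effect size or interval width, so there is no stated figure to reproduce on this point. The sample size comes from the Sample section: 35 couples per group, 70 in total. The recruitment figures agree with it roughly: 370 × 0.35 × 0.75 × 0.70 = 68.0 couples. With the 7% loss in the Procedures section, 70 × 0.93 = 65.1 couples are analysed.

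**Assumptions not in the document.** Outcome SD 1; baseline-outcome correlation 0.6; source explaining a share s of the variance left after baseline, with s from 0 to 30%; 2, 4 or 10 strata; two-sided 95% intervals.

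**Approximation.**

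1. Residual SD after baseline: √(1 − 0.6²) = 0.8.
2. Standard error from the stated model: 2 × 0.8 / √65.1 = 0.198.
3. Standard error with source in the model: 0.198 × √(1 − s), before the small loss of degrees of freedom.
4. Ratio of widths, stated model to model with source: 1 / √(1 − s). This gives 1.00, 1.01, 1.03, 1.05, 1.12 and 1.20 at s = 0, 2, 5, 10, 20 and 30%.

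**Simulation.** Each cell has 4,000 runs of 70 couples in permuted blocks of 4 and 6 within source, with 7% random loss and no treatment effect. Group + baseline is compared with group + baseline + source.

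| Share s | Width ratio, 2 strata | 4 strata | 10 strata | Coverage of stated model's 95% interval (2 / 4 / 10 strata) |
|---|---|---|---|---|
| 0% | 1.00 | 1.00 | 0.98 | 95.2 / 94.5 / 95.0% |
| 2% | 1.01 | 1.01 | 0.99 | 95.4 / 95.3 / 95.2% |
| 5% | 1.03 | 1.02 | 1.01 | 95.9 / 95.5 / 95.7% |
| 10% | 1.05 | 1.05 | 1.03 | 95.7 / 96.0 / 95.6% |
| 20% | 1.12 | 1.12 | 1.10 | 97.1 / 96.6 / 96.7% |
| 30% | 1.20 | 1.19 | 1.17 | 97.4 / 97.7 / 97.9% |

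With source in the model, coverage stays between 94.5% and 95.6% in every cell.

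**Reading the table.**

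- The simulation agrees with the formula for few strata.
- The stated model's standard error can also be set against the actual spread of its own estimates. With 2 strata the mean standard error is 0.200 against an empirical SD of 0.192 at s = 10% (ratio 1.04) and 0.173 at s = 30% (ratio 1.16). This gap is a little smaller than the width ratio, because incomplete blocks and losses leave some imbalance between arms, which only adjustment removes.
- With 10 strata and s of 2% or less, the ratio is below 1. Adjustment then makes the interval 1 to 2% wider, since nine degrees of freedom are spent for little return.

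**The case against.** The case against has four parts.

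- **The effect is conditional.** Baseline anxiety is already in the model and absorbs source differences that persist from entry. Nothing in the document shows that source matters beyond that. This stands: a reader might infer that the intervals will certainly be too wide, and the document does not support it. The excess may be nil.
- **The covariate list may not be complete.** The article condenses a fuller plan and calls group the main predictor. An analysis plan that is not shown could add source. This stands in part. The article does name its covariate, stratification is a feature of its own design, and nothing in it brings the two together.
- **The blinding sentence is not a firm bar.** A reader might infer that the statistician could not add source under the plan. The same sentence withholds group, without which no ANCOVA can be run, so some coded release must be intended, and source could be released in the same way. The sentence also speaks of site where the randomisation section speaks of source, and the article does not equate the two. It needs clarifying.
- **Little depends on it.** The error is on the cautious side, feasibility is the first aim, and no significant difference is expected. This stands and limits the weight of the point. A reader might infer a biased estimate or excess false positives; neither follows.

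**Conclusion.** The point holds as a conditional loss of precision. The stated model does not reflect the stratified randomisation. Where source is prognostic beyond baseline, its intervals are conservative and the estimate is unbiased. Against a model with source, the excess width is about 0 to 3% for a residual-variance share of 0 to 5%, and about 5%, 12% and 20% for shares of 10%, 20% and 30%. These sizes rest on assumed shares and a small number of strata, and the article gives neither. With 10 strata they are slightly smaller, and they reverse by 1 to 2% when source explains almost nothing. Recruitment through clinics in two states and through the media makes some difference between sources plausible, but its size is unknown. The change is worth making because it is cheap; the pilot's results are not invalid without it.

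**What to change.** 1. In the Data analysis section, add recruitment source as a covariate in every ANCOVA, primary and secondary, for patients and for partners.
2. Before unblinding, fix a few source categories and a rule for pooling small ones, so that many sparse strata do not use up degrees of freedom.
3. In the Blinding section, state that the statistician receives group (A/B) and source category (1, 2, 3 and so on) as codes without their meaning. This keeps the blinding and also settles how group reaches the analysis. Say there whether site and source are the same thing.

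The cost is one more covariate, one masked data column and a sentence or two of text. Each source category beyond the first uses one degree of freedom: three categories would leave about 60 of the 62 available with 65 couples (65 − 3 = 62 under the stated model; 65 − 5 = 60 with source).

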### Process evaluation

Process evaluation will explore the intervention’s implementation and receipt [93]. Following their last data collection point, a process evaluation, semi-structured phone interview will be scheduled with consenting *Coping-Together* and MEC couples (consent obtained at baseline) to explore their views on, and opinions about, the *Coping-Together* or MEC material used and obtain feedback on the study’s process and procedures. Interviews will be audio-recorded and transcribed verbatim. For consistency, a couple’s process evaluation interview will be completed by the same research assistant that conducted their follow-up phone calls. The interview is anticipated to last 45–60 minutes. A script will be used to open and focus the discussion and prompts will be specified to help the interviewers to further elaborate on the study’s topics, if needed. All transcripts will be reviewed line-by-line and words, statements, or paragraphs pertaining to participants’ opinions about the *Coping-Together* or MEC material or the study will be coded. Interpretation and clustering of the codes will result in detecting themes and patterns. Transcripts will be coded by two research team members and emerging findings will be discussed at regular team meetings.

## Discussion

Partners’ anxiety rates exceed not only the Australian norm, but also those of cancer survivors themselves [5]. Hence, it is imperative that coping skills interventions target the couple as a unit and enhance both patients’ and partners’ ability to overcome cancer challenges. Recent reviews support the efficacy of coping skills training interventions in optimising patients' illness adjustment [26,94]. However, these interventions tend to be led by highly trained health professionals; considerably limiting their long-term sustainability, due to high cost and limited availability of qualified professionals, especially in non-metropolitan areas. In addition, it is recognised that patients who might benefit from conventional face-to-face psychosocial interventions do not access these, either by preference or because of geographical or mobility barriers [34,35]. Self-directed (also referred to as self-help or self-administered) interventions overcome these limitations, are acceptable to patients and efficacious in decreasing patients’ distress [34]. *Coping-Together* is a novel psychosocial intervention, as it targets both patients and their partners, translates up-to-date research on effective coping and renders it readily available to couples for their use where and when they need to, and actively engages couples in learning new coping skills. To our knowledge, *Coping-Together* is the first, self-directed intervention for couples affected by cancer.

### Implications

*Coping-Together* has the potential to have a direct impact on the psychological well-being of patients and their partners and to redress issues of access and equity for couples from regional, rural and remote areas, without burdening an already stretched oncology workforce. This pilot trial will investigate the feasibility and potential efficacy of *Coping-Together* in reducing the negative psychosocial impact of cancer on patients and their partners, which in turn will be used to design a larger trial that will not only examine the efficacy of *Coping-Together*, but also its direct cost and cost-effectiveness. Findings from this study will also contribute to the larger literature in advocating for psychosocial care in the acute post-diagnostic phase and in identifying individual and couple-level factors that contribute to patients’ and partners’ coping, anxiety, and use of self-directed resources. If future studies support the efficacy of *Coping-Together*, the intervention’s low production cost and self-directed nature will contribute to its ready integration into existing supportive care infrastructures for patients diagnosed with prostate cancer and their partners.

## Abbreviations

NHMRC: National Health and Medical Research Council; PST: Problem-solving therapy; MEC: Minimal ethical care; QOL: Quality of life; DT: Distress Thermometer; HADS: Hospital Anxiety and Depression Scale; AQoL-8D: Assessment of Quality of Life – 8 dimensions; CASE-Cancer: Communication and Attitudinal Self-Efficacy Scale for cancer scale; PPCI: Profile of Preferences for Cancer Information; ANCOVA: ANalysis of COVAriance.
